### 2.2. Sample Size Calculation

In this procedure, the total score of the Montreal Cognitive Assessment Scale was invoked as the main effect index. The effect value was 0.9 in the treatment group and 0.725 in the control group [17], 0.8 in power and 0.05 in alpha. The sample size was estimated at PASS 24.0 software to be 116 cases, i.e., 58 cases in each group. Allowing 20% dropout rate, the total sample size was expected to be 140 patients (70 in each group).

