### 2.8. Randomization and Allocation

After meeting the selection criteria, 140 eligible participants will be randomly assigned to the EA group and the CG group in a 1 : 1 allocation ratio. The random grouping sequence will be performed according to a random list of numbers generated by the randomization center of Ningxia Medical University and hidden by the opaque and closed envelope. The random sequence will be managed by specific personnel who contact no participant and are not involved in the data collection or analysis.

All participants will receive the following free services, including assessment, functional magnetic resonance imaging (both EA group and CG group), health education (both EA group and CG group), and EA treatment (only EA group) and should adhere to all assessment and treatment schedules as much as possible.

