### 3.10. Statistical Analysis

IBM SPSS Statistics 24.0 software will be used to conduct the whole data analysis by an independent statistician who is unaware of group assignments. All continuous variables will be presented as mean ± standard deviation (SD), and categorical variables will be presented as numbers (%). The statistical significance level is considered to be 95% CIs (two-sided alpha *P* < 0.05).

The effect of the intervention will be assessed as the change in outcome measures between the baseline and eight weeks (after treatment sessions end), using a repeated-measures analysis of variance (ANOVA) and chi-square test.

The difference in effect between the CG group and the EA group will be assessed by comparing changes in the MoCA score and secondary outcomes including language learning and memory function, attention function, executive function, and visuospatial function using the independent *t*-test or Mann–Whitney *U* test on continuous variables and chi-square test or Fisher's exact test on categorical variables.

Intention-to-treat analyses will be used for all outcomes. A multiple imputation method will be carried out to fill in missing data for outcomes.

The structure and function of functional magnetic resonance will be analyzed by SPM software based on the MATLAB platform. Neural network analysis techniques such as VBM, ROI, and ICA will be used to compare the differences in functional connectivity changes between groups by independent sample *t*-test. FDR correction will be used for multiple comparison and correction.

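### The 20% dropout allowance does not lead from 116 required to 140 randomised: losing 20% of 140 leaves 112 patients, 4 fewer than the calculation requires

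*Protocol article*

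**What the plan says.** Section 2.2 (Sample Size Calculation) gives the requirement before dropout: "The sample size was estimated at PASS 24.0 software to be 116 cases, i.e., 58 cases in each group". The next sentence adds the allowance: "Allowing 20% dropout rate, the total sample size was expected to be 140 patients (70 in each group". Section 2.8 confirms equal arms, with patients "randomly assigned to the EA group and the CG group in a 1 : 1 allocation ratio".

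The inflation formula is not stated. The abstract and sections 2.1, 2.3 and 2.8 repeat the total of 140. No section gives a different dropout rate or a reason why fewer than 116 patients would be enough. Section 2.7 defines dropouts as patients who leave for certain serious adverse events, a further stroke after enrolment, or voluntary withdrawal. For missing outcomes, section 3.10 says: "A multiple imputation method will be carried out to fill in missing data for outcomes".

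**The concern.** A dropout allowance exists so that the required number of patients remains after the expected losses. Taking 20% off 140 does not leave 116, so the three printed figures (116 required, 20% dropout, 140 randomised) do not fit together if the rate is a share of those randomised.

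At stake is whether the design delivers the 80% power it states. If dropout is exactly what the protocol expects, the trial finishes below its own requirement. A reader who judges retention against 20% would accept 28 losses as planned for, when only 24 can be absorbed.

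**Working it through.** **Inputs, all from section 2.2 except the allocation ratio (section 2.8)**
- Required: 116 in total, 58 per group
- Dropout rate: 20%
- Randomised: 140 in total, 70 per group
- Allocation: 1:1

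**Step 1. Reproduce the printed 140.**
- Multiplying, N × (1 + d): 116 × 1.20 = 139.2, rounded up to 140. Per group, 58 × 1.20 = 69.6, rounded up to 70. Both match the protocol.
- Dividing, N / (1 − d): 116 / 0.80 = 145. Per group, 58 / 0.80 = 72.5, rounded up to 73, so 146 in total. Neither matches.

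The printed figure therefore comes from adding 20% to the required number.

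**Step 2. Apply the stated rate to the stated N.**
- 140 × 0.80 = 112, or 56 per group.
- Shortfall: 116 − 112 = 4 in total, 2 per group.

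**Step 3. Find the dropout rate that 140 can absorb.**
- (140 − 116) / 140 = 24 / 140 = 17.1%.

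**Step 4. Effect on power.** Section 2.2 gives no standard deviation or standardised difference, so this step needs an assumption: that the 116 came from a two-sided 5% two-sample t-test.
- If 58 per group gives exactly 80% power, the implied standardised difference is d = 0.525. Power at 56 per group is then 78.6%, a loss of about 1.4 points. The normal approximation (d = 0.520) also gives 78.6%.
- If 58 is simply the first whole number to reach 80%, the true power at 58 may be slightly above 80%. Allowing for this, power at 56 per group lies between 78.6% and 79.3%.

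**Step 5. Chance of keeping 116.** Assume each patient drops out independently with probability 0.20. The chance that at least 116 remain is then:

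| Randomised | P(at least 116 remain) |
|---|---|
| 140 | 23% |
| 145 | 55% |
| 146 | 61% |

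An allowance based on the expected loss misses its target fairly often even when done correctly, so the 23% should be read against 55% to 61%, not against 100%.

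**The case against.** **The 20% may have been meant as an addition to 116.** Section 2.2 gives no formula and does not explicitly promise that 116 remain after losses, and read this way the figures reproduce. That explains how 140 arose, but it does not make the sentence right. The text calls the 20% a dropout rate, and section 2.7 defines dropouts among patients already enrolled, so the natural denominator is those randomised. On that basis 140 covers 17.1%.

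**Dropping out is not the same as having no final MoCA score.** Section 2.7 does not say whether dropouts are still assessed, and section 3.10 plans intention-to-treat analysis. This stands in part: if some dropouts return for the final assessment, more than 112 patients will have data. But the allowance in section 2.2 only makes sense if dropouts are counted as lost, so the sizing must be judged on that footing.

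**Multiple imputation keeps everyone in the analysis.** It does, but Table 1 schedules the outcome measures only before enrolment and at week 9. With no intermediate score, imputing a missing final value recovers little information beyond the completers.

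**The power figure is conditional.** This stands. Section 2.2 says only: "The effect value was 0.9 in the treatment group and 0.725 in the control group", with "0.8 in power and 0.05 in alpha", and does not state the scale of the two values. If they are read as proportions, a two-sided 5% test at 80% power needs about 75 to 77 per group without continuity correction. About 58 per group arises only with a one-sided test, whereas section 3.10 specifies a two-sided alpha. The basis of the 116 is a separate question. The inflation step is wrong whatever the starting number.

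**No rule in the protocol makes 20% a retention threshold.** Also correct. Retention is not among the monitoring board's listed tasks in sections 3.9 and 3.11, so no formal decision hangs on the figure.

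**Conclusion.** The concern holds. Taking 116 and 20% as printed, and the dropout rate as a share of those randomised, 140 is too few by 5 patients (6 with equal arms). The expected number remaining is 112 instead of 116, and the real tolerance is 17.1%. This part is arithmetic on the protocol's own figures.

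The consequence is modest. Power falls from 80% to between 78.6% and 79.3%, on the assumptions that 58 per group does give 80% in a two-sided t-test and that dropouts contribute no final score. Section 2.2 should be corrected because it states a property the design does not have, but the shortfall alone does not threaten the trial.

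**What to change.** Keep 140 and correct the sentence in section 2.2 in one of two ways:

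1. State that randomising 140 (70 per group) leaves 58 evaluable patients per group for dropout up to about 17% (24 of 140).
2. Keep the 20% rate, state that 56 evaluable patients per group are expected, and report the power at that number. The sponsor must recalculate this from its own effect size and variance, because the article does not give enough to do so.

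The first option needs no further input. The alternative of keeping both 20% and 116 would mean randomising 146 (73 per group), 6 more than planned, which is hard to justify for a loss of about 1.4 points of power.

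Either rewording costs one sentence, with no extra patients and no change in conduct or analysis. The only downside is a slightly less favourable stated tolerance or power. Because option 1 repeats 58 per group as the requirement, the basis of that number should be confirmed at the same time.

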### 2.3. Participants and Recruitment

A total of 140 right-handed participants will be recruited from community VCIND patients in Yinchuan, Ningxia Hui Autonomous Region, China. Eligible patients must comply with the inclusion and exclusion criteria. Participants were recruited through multimodal strategies, including print advertisements, WeChat, volunteer recommendation, and community publicity. All participants will undergo a baseline evaluation, including complete sociodemographic and clinical data collection. Meanwhile, all participants will be invited to voluntarily sign the informed consent.

### 2.4. Diagnostic Criteria

Compiling Guidelines for Diagnosis and Treatment of Vascular Cognitive Impairment with Reference to the Neurological Society of Chinese Medical Association [18].

(1) Cognitive impairment: the main complaint or informed person-reported cognitive impairment, and objective examination also had evidence of cognitive impairment, and/or objective examination confirmed that cognitive function was lower than before. (2) Vascular factors: including vascular risk factors, history of stroke, focal signs of nervous system, and evidence of cerebrovascular disease shown by imaging, not necessarily all of the above. (3) There is a causal relationship between cognitive impairment and vascular factors. (4) The daily ability is basically normal, but the complex instrumental daily ability can have slight damage. (5) It does not meet the diagnostic criteria of dementia.

### 2.5. Inclusion Criteria

Patients aged 50–75 years who (1) meet the diagnostic criteria of VCIND described above; (2) MoCA score of 18–26 [19, 20]; (3) are right-handed; (4) elapsed time after stroke ≥6 months; (5) have no acupuncture treatment in the last six months; and (6) volunteer to participate in the research and sign the informed consent were included in the study.

### 2.6. Exclusion Criteria

Patients who (1) have awareness disorders, severe visual, hearing, and aphasia, and other health assessment failures; (2) have memory and executive dysfunction caused by vascular dementia, Alzheimer's disease, hypothyroidism, brain trauma, etc.; (3) have comorbidity including tumors and severe heart, liver, kidney, hematopoietic system, and endocrine system diseases; (4) have psychiatric history, such as personality disorders and schizophrenia; and (5) have cognitive impairment caused by depression, Baker Depression Scale (>10 points) will be excluded from the study.

### 2.7. Dropout Criteria

Patients who (1) have serious adverse events, which are not advisable to continue the experiment; (2) have a secondary stroke after enrollment; and (3) quit the RCT voluntarily will be considered as having dropped out.

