### 3.6. Primary Outcome

The primary outcome of this study is the changes in the score on MoCA from baseline to 8 weeks after intervention between the two groups and within groups. It is widely used for cognitive function assessment and can reflect the whole cognitive level of individuals. The MoCA has a maximum score of 30 points divided into eight parts, namely, visual space/executive ability (5 points), name (3 points), memory (5 points), attention (3 points), computing (3 points), language fluency (3 points), abstraction (2 points), and orientation (6 points). MoCA has excellent reliability and validity and is sensitive enough for clinical and research practice [25].

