### 3.12. Investigation of Adverse Events and Safety

During the acupuncture treatment, subjects will be informed about adverse events such as local bleeding, subcutaneous hematoma, or pain associated and serious adverse events such as dizziness and palpitation in advance. Any adverse events and serious adverse events during treatment will be reported in the Case Report Form (CRF) and investigated, including its type and frequency, and appropriate treatments for the associated symptoms will be provided immediately to minimize serious adverse events. If a serious adverse event occurs, the case will be reported to the Data and Safety Monitoring Board (DSMB) of the clinical evaluation center of the General Hospital of Ningxia Medical University immediately and the blinding code will be broken. If necessary, even part or all of the trial will be suspended until further instructions are expected to be available. We will pay for the treatment of the subjects with serious adverse events until recovery.

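### Second stroke and some serious adverse events count as dropout, so these participants' post-treatment MoCA would probably be imputed from people who had no such event

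*Protocol article*

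**What the plan says.** Section 2.7 (Dropout Criteria) names three kinds of dropout. The first covers patients who "have serious adverse events, which are not advisable to continue the experiment". The other two are patients who "have a secondary stroke after enrollment; and (3) quit the RCT voluntarily will be considered as having dropped out". A health event and a free decision to leave are therefore put on the same footing, and the rule makes no distinction between arms.

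Section 3.10 (Statistical Analysis) then states: "Intention-to-treat analyses will be used for all outcomes. A multiple imputation method will be carried out to fill in missing data for outcomes". It does not treat missing outcomes differently by reason for dropout.

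Three other places bear on the point:

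- Section 3.6 defines the primary outcome as "changes in the score on MoCA from baseline to 8 weeks after intervention between the two groups and within groups", so both a between-group and a within-group result are primary.
- Table 1 schedules MoCA once before enrollment and once after the intervention. For dropouts it schedules only the recording of reasons, during the intervention period.
- Section 2.2 raises the sample size from 116 to 140 for 20% dropout.

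**The concern.** Intention-to-treat analysis aims to compare all randomised patients as they actually fared. That needs the outcome of patients who had a bad course, and here a second stroke is such a course. The participants have a vascular cognitive disorder, the primary outcome is a cognitive score, and a further stroke can lower that score directly.

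If a second stroke ends a person's participation, the missing MoCA is missing for a reason tied to its own value. There is no intermediate MoCA to show the decline. If nobody is assessed after a stroke, the trial holds no post-stroke MoCA at all, and a model fitted to the observed data cannot learn what a stroke does to the score, even with stroke as a predictor. The imputed values then describe a trial in which nobody had the event.

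The fault would lie in the dropout rule and in data collection, and an analysis plan could not repair it afterwards. Section 3.13 says that recruitment and intervention are still under way, so these MoCA scores can still be collected.

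**Working it through.** **1. Does dropping out mean no outcome?** The text has to be read together, because no sentence settles it.

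- Section 2.7 speaks of continuing the experiment, not the treatment.
- The rule covers both arms. Control participants receive only weekly health education on top of basic treatment (section 3.3). They have no electroacupuncture to stop, so for them dropout can hardly mean only stopping treatment.
- The sample-size allowance reproduces as 116 × 1.20 = 139.2, rounded up to 140 (58 × 1.20 = 69.6, rounded up to 70 per arm). Such an allowance makes sense only if dropouts are expected to give no primary outcome. Whether multiplying by 1.20 is the right inflation is a separate question.
- Table 1 describes no outcome visit for people who have dropped out.

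Together these imply, without stating it, that such participants have no post-treatment MoCA.

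**2. What imputation would then do.** Let p be the proportion of an arm with an event, L the mean MoCA loss from the event, and μ the mean change in event-free participants.

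- Mean change if everyone is assessed: μ − pL
- Mean change if the missing scores are imputed from event-free participants of the same arm: μ
- Overstatement of the within-group change: pL
- Shift in the EA-minus-control difference: p(EA) × L(EA) − p(CG) × L(CG), which is [p(EA) − p(CG)] × L when the loss is the same in both arms

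**3. Numbers.** The documents give no event rates and no MoCA loss, so every p and L below is an assumption. With 70 per arm, 3% is 2.1 people, 6% is 4.2 and 10% is 7.

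Within-group, p = 3% and L = 4: 0.03 × 4 = 0.12 points.

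Between-group shift in MoCA points (positive favours EA):

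| Events EA / control | L = 2 | L = 4 | L = 6 |
|---|---|---|---|
| 3% / 3% | 0 | 0 | 0 |
| 5% / 2% | +0.06 | +0.12 | +0.18 |
| 10% / 3% | +0.14 | +0.28 | +0.42 |
| 3% / 6% | −0.06 | −0.12 | −0.18 |

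For example, (0.10 − 0.03) × 6 = +0.42 and (0.03 − 0.06) × 6 = −0.18.

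**4. Check by simulation.** Assumptions: 70 per arm, a true difference of 1.0 point in event-free people, SD of change 2.5, L = 4, and multiple imputation within arm from baseline MoCA using event-free participants, with 1,500 repeats. The simulation error of each mean is about 2.5 × √(2/70) ÷ √1500 = 0.01.

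| Events EA / control | Difference with actual scores | Difference after imputation |
|---|---|---|
| 3% / 3% | 0.99 | 1.00 |
| 5% / 2% | 0.88 | 0.99 |
| 10% / 3% | 0.73 | 1.00 |
| 3% / 6% | 1.13 | 1.01 |

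Imputation returns the event-free effect of 1.0 every time. The gap between the columns agrees with the formula, within simulation error.

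**The case against.** The strongest reply is that the plan never says assessment stops. Section 2.8 asks all participants to keep to the assessment schedule as far as they can, and section 3.10 applies intention-to-treat to every outcome. Pairing intention-to-treat with multiple imputation is standard, and the imputation model may properly be left to an analysis plan. This stands in part. A reader might infer that the plan contradicts its own intention-to-treat statement, or that poor scores are certain to be replaced. The documents do not support either, because the result depends on whether dropouts are assessed. The general request in section 2.8, however, is not a commitment to assess people already classed as dropouts, and no imputation model can make up for having no post-stroke score.

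A reader might also infer that every serious adverse event leads to removal. Section 2.7 limits this to events after which continuing is inadvisable.

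A third tempting inference is that the bias favours EA, because section 3.12 mentions "serious adverse events such as dizziness and palpitation" in connection with acupuncture. This joins two different groups. Dizziness and palpitation may be more frequent in the EA arm, but nothing in the documents says that they lower MoCA. A second stroke plausibly lowers MoCA, but nothing says that it is more frequent under EA. Bias in the comparison needs arms that differ in event rate or in loss, and the fourth row of the tables shows that it can go against EA. This objection stands in full.

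**Conclusion.** The concern holds in a conditional form. If participants classed as dropouts under section 2.7 are not assessed, which is the natural but unstated reading, imputation estimates their MoCA from people without the event. The result then describes a trial without such events and not all randomised patients as they fared. The point rests mainly on second stroke.

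The within-group change is overstated whenever events that lower MoCA occur, even with balanced arms. The between-group difference shifts only if rates or losses differ. Within the ranges tried the shift is a few tenths of a point at most, and its direction is not established. The 10% rate behind the largest figure means 7 of 70 people with a damaging event during an 8-week intervention, which is an extreme case.

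These shifts cannot be stated as a share of the difference that the trial is powered to detect, because section 2.2 gives neither a MoCA standard deviation nor a difference in MoCA points. Severity is moderate: the missing data are avoidable and easily prevented, but neither the size nor the sign of a bias is shown.

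**What to change.** Amend section 2.7 so that stopping study treatment and leaving the study are separate:

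- Count as dropout only participants who withdraw consent to assessment or cannot be assessed.
- Collect the scheduled post-treatment MoCA from everyone else, including those with a second stroke or a serious adverse event.
- Analyse all participants in the arm to which they were randomised.
- Limit multiple imputation to what is still missing after that.

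No decision on anyone's treatment changes. Some people will be too ill to be tested after a stroke, so some informative missingness will remain. A sensitivity analysis that does not assume missing at random would address this; it is optional and may be left to the analysis plan.

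The cost is a short amendment and a few assessments of people who have stopped treatment, at a visit already in Table 1. The estimate may come out less favourable. Section 3.12 has the blinding code broken after a serious adverse event, so the MoCA assessor of such a participant should be kept unaware of the allocation.

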### 2.8. Randomization and Allocation

After meeting the selection criteria, 140 eligible participants will be randomly assigned to the EA group and the CG group in a 1 : 1 allocation ratio. The random grouping sequence will be performed according to a random list of numbers generated by the randomization center of Ningxia Medical University and hidden by the opaque and closed envelope. The random sequence will be managed by specific personnel who contact no participant and are not involved in the data collection or analysis.

All participants will receive the following free services, including assessment, functional magnetic resonance imaging (both EA group and CG group), health education (both EA group and CG group), and EA treatment (only EA group) and should adhere to all assessment and treatment schedules as much as possible.

